## Abstract

**Background:**

Chronic Insomnia Disorder (CID) is highly prevalent among older adults and impairs cognitive function. Insomnia accelerates the progression of mild cognitive impairment (MCI) and increases the risk of developing dementia. Acupuncture has been demonstrated in improving sleep quality and cognitive function. This study aims to explore the functional brain characteristics of CID with MCI patients and to assess the effects of acupuncture therapy using functional near-infrared spectroscopy (fNIRS).

**Methods and design:**

This study is a single-center randomized controlled trial. Participants will be randomly assigned to the manual acupuncture group or the placebo acupuncture group for an 8-week intervention period. fNIRS data will be collected during resting test and working memory test at baseline and at end of the intervention. The primary outcome is the change of the Montreal Cognitive Assessment (MoCA) score, secondary outcomes include the change of Mini-Mental State Examination (MMSE), Insomnia Severity Index (ISI), Patient Health Questionnaire-9 (PHQ-9), Generalized Anxiety Disorder Scale (GAD-7), and Apathy Evaluation Scale-Informant (AES-I).

**Discussion:**

The results of the study will provide insights into the effects of acupuncture on sleep quality and cognitive performance in CID with MCI patients. By utilizing fNIRS technology, we will elucidate the neural functional characteristic underlying the therapeutic benefits of acupuncture.

**Clinical trial registration:**

https://ClinicalTrials.gov, identifier ChiCTR2300076182.

## Introduction

1

The burden of dementia is expected to increase rapidly due to the aging population. It is estimated that more than 150 million people will suffer from dementia by 2050. Efforts have been focused on the pre-dementia stage, known as mild cognitive impairment (MCI). Identifying potential risk factors is a crucial strategy to reduce the incidence of dementia. Chronic insomnia disorder (CID) affecting approximately 10–20% of the population, with older adults being particularly susceptible (1). Researchers found that chronic insomnia is a critical risk factor for cognitive decline. Older adults with insomnia face a greater risk of MCI compared to those with normal sleep patterns. MCI affects memory, language comprehension, cognitive processing, and decision-making abilities. It represents a stage preceding dementia. Abnormal sleep patterns disrupt biochemical and physiological functions associated with the nervous system (2). Evidence supports that chronic insomnia is an independent risk factor for cognitive decline (3), leading to neuroinflammation, oxidative stress, neuronal apoptosis, and amyloid-*β* (Aβ) buildup, which contribute to memory impairment and cognitive decline (4, 5). Recent studies have emphasized the link between sleep quality and brain aging. Chronic insomnia leads to cortical gray matter decline and subcortical structural atrophy, potentially contributing to the onset of MCI (6).

Short-term conversion rates from MCI to dementia range from 20 to 40%, while long-term rates over 5–10 years reach 60–100% (7–9). It is essential to prevent the onset and implement early interventions to delay its progression. Medications for dementia and other neurodegenerative diseases, including cholinesterase inhibitors, N-methyl-D-aspartate (NMDA) receptor antagonists, neurotrophic promoters, antioxidants, and anti-inflammatory drugs. However, the high costs and severe side effects resulting in low patient adherence (10). A trial showed the efficacy of a specific medication, Lecanemab, noted adverse events such as cerebral edema, infusion reactions, atrial fibrillation, syncope, and angina pectoris (11).

Acupuncture has shown effects in enhancing sleep quality and cognitive function, reducing fatigue, regulating emotions, and improving quality of life (12–14). It protects neural function by alleviating inflammation, modulating metabolism, controlling memory-related factors, and activating the brain cortex to reduce neuronal apoptosis (15–17). Acupuncture is one of the most often used adjuvant therapies for MCI patients (12). It has been widely used to improve cognitive function, with many studies confirming its efficacy (14–16). according to a previous NMA study, acupuncture may be the efficacy and safe complementary and alternative therapy for improving cognitive function in people with MCI (13).

In early stage, patients may not exhibit obvious brain structure changes, but neural network function has already altered. Thus, it is essential to explore the mechanisms from the perspective of brain function. Advances in imaging techniques and acupuncture research have led to increased exploration of the brain’s functional mechanisms affected by acupuncture therapy for neurodegenerative diseases (18). Reviews have noted widespread abnormalities in brain network connectivity and damage in brain regions during cognitive decline (19). Observations via neuroimaging indicate that acupuncture activates cortical functional brain areas, enhances blood flow, regulates brain networks, and improves visual–spatial function (20).

Functional near-infrared spectroscopy (fNIRS) detects changes in brain function by measuring the absorption of near-infrared light by oxygenated (HbO) and deoxygenated hemoglobin (HbR). It provides high resolution without invasive procedures or significant motion interference (21, 22). This technology facilitates monitoring of brain region activity and connectivity (23, 24). Previous studies (25, 26) have found changes in brain functional imaging in insomnia and cognitive decline individuals, and acupuncture could regulate these changes (27). Prior study has confirmed that CID patients exhibit working memory deficits related to cognitive levels with altered connectivity patterns change between the frontal and temporal regions. It possibly serving as the neural basis of cognitive impairment (28). Additionally, acupuncture can modulate network patterns in the frontal and temporal lobes of insomnia patients (29). Evidence supports that acupuncture is benefit to sleep quality and cognitive enhancement, but brain imaging characteristics and solid proof from clinical trials are lacking. Based on the background, this study aims to investigate the brain functional characteristics of CID with MCI patients using fNIRS technology, and assess the changes following acupuncture intervention.

## Objectives

2

This study aims to assess the activation patterns and functional connectivity in the frontal and temporal brain regions of CID with MCI patients and identify the effects of acupuncture on brain function related to sleep and cognitive performance.

## Methods

3

### Study design

3.1

This is a randomized, single-blind, placebo controlled clinical trial. This study will be conducted at the Affiliated Hospital of Chengdu University of Traditional Chinese Medicine. Reporting of the protocol will adhere to the Standards for Reporting Interventions in Clinical Trials of Acupuncture (STRICTA) guidelines (30) (Table 1) and the Consolidated Standards of Reporting Trials (CONSORT) 2010 Checklist (31) (Table 2).

**Table 1 tab1:** STRICTA 2010 checklist of information to include when reporting interventions in a clinical trial of acupuncture (expansion of item 5 from CONSORT 2010 checklist).

Item	Item number	Detail
1. Acupuncture rationale	(1a) Style of acupuncture (e.g., Traditional Chinese Medicine, Japanese, Korean, Western medical, Five Element, ear acupuncture, etc.)	Traditional Chinese Medicine (TCM)
	(1b) Reasoning for treatment provided, based on historical context, literature sources, and/or consensus methods, with references where appropriate	The treatment is based on traditional Chinese medicine acupuncture theory, literature support, and expert consensus
2. Details of needling	(1c) Extent to which treatment was varied	Standardized acupuncture treatment
	(2a) Number of needle insertions per subject per session	Twelve
	(2b) Names of points used	GV20 (Baihui), EX-HN1 (Sishencong), GV24 (Shenting), HT7 (Shenmen), GB39 (Xuanzhong), and KI4 (Dazhong)
	(2c) Depth of insertion, based on a specified unit of measurement, or on a particular tissue level	From 10 to 40 mm
	(2d) Response sought (e.g., de qi or muscle twitch response)	Deqi (soreness, tingling, heaviness, distention, etc.)
	(2e) Needle stimulation (e.g., manual, electrical)	Manual acupuncture
	(2f) Needle retention time	30 min
	(2 g) Needle type (diameter, length, and manufacturer or material)	Sterile, disposable acupuncture needles (diameter, 0.25 mm; length,25/40 mm; Hwato, China)
3. Treatment regimen	(3a) Number of treatment sessions	24 sessions
	(3b) Frequency and duration of treatment sessions	3 sessions a week (every other day), for a total of eight weeks
4. Other components of treatment	(4a) Details of other interventions administered to the acupuncture group (e.g., moxibustion, cupping, herbs, exercises, lifestyle advice)	Track the regular usage of sleep medications and provide guidance for daily living
	(4b) Setting and context of treatment, including instructions to practitioners, and information and explanations to patients	The trial will be conducted at the Department of Preventive Treatment at Chengdu University of TCM. Researchers will diagnose and give informed consent to the participants, the acupuncturist will be responsible for providing treatment and lifestyle advice, and designated researchers will be responsible for randomization and data collection. All participants of the acupuncture group will be arranged to the acupuncture room for treatment
5. Practitioner background	Description of participating acupuncturists (qualification or professional affiliation, years in acupuncture practice, other relevant experience)	Trained, licensed acupuncturists with at least 2 years in acupuncture clinical practice
6. Control or comparator interventions	(6a) Rationale for the control or comparator in the context of the research question, with sources that justify this choice	The aim of setting the placebo acupuncture as a control group is to explore the specific effects of manual acupuncture on participants
	Precise description of the control or comparator. If sham acupuncture or any other type of acupuncture-like control is used, provide details as for items 1 to 3 above	In the control group, operators stimulate the same acupoints as the manual acupuncture group for 8 weeks, 3 sessions a week (every other day), with the use of PSD + retractable blunt needles. Except for the operators, every one of the participants in the study is blind to the intervention.

**Table 2 tab2:** CONSORT 2010 checklist with the Non-pharmacological Trials Extension to CONSORT (with STRICTA 2010 extending CONSORT Item 5 for acupuncture trials)

Section/Topic	Item	CONSORT 2010 Statement: Checklist item	Page
TITLE AND ABSTRACT			
	1.a	Identification as a randomized trial in the title	1
	1.b	Structured summary of trial design, methods, results, and conclusions; for specific guidance see CONSORT for Abstracts	1
INTRODUCTION			
Background and objectives	2.a	Scientific background and explanation of rationale	2
	2.b	Specific objectives or hypotheses	2
METHODS			
**Trial design**	3.a	Description of trial design (e.g., parallel, factorial) including allocation ratio	2
	3.b	Important changes to methods after trial commencement (e.g. eligibility criteria), with reasons	5
Participants	4.a	Eligibility criteria for participants	5
	4.b	Settings and locations where the data were collected	5
**Interventions**	5	The interventions for each group with sufficient details to allow replication, including how and when they were actually administered	6-7
Outcomes	6.a	Completely defined pre-specified primary and secondary outcome measures, including how and when they were assessed	7-9
	6.b	Any changes to trial outcomes after the trial commenced with reasons	10-11
Sample size	7.a	How sample size was determined	3
	7.b	When applicable, explanation of any interim analyses and stopping guidelines	5
Randomization			
Sequence generation	8.a	Method used to generate the random allocation sequence	5
	8.b	Type of randomization; details of any restriction (e.g., blocking and block size)	5
Allocation concealment	9	Mechanism used to implement the random allocation sequence (e.g., sequentially numbered containers), describing any steps taken to conceal the sequence until interventions were assigned	5
Implementation	10	Who generated the random allocation sequence, who enrolled participants, and who assigned participants to interventions	12
**Blinding**	11.a	If done, who was blinded after assignment to interventions (e.g. participants, care providers, those assessing outcomes) and how	5
	11.b	If relevant, description of the similarity of interventions	6-7
**Statistical methods**	12.a	Statistical methods used to compare groups for primary and secondary outcomes	10-11
	12.b	Methods for additional analyses, such as subgroup analyses and adjusted analyses	10-11
RESULTS			
Participant flow (A diagram is strongly recommended)	13.a	For each group, the numbers of participants who were randomly assigned, received intended treatment, and were analyzed for the primary outcome	2-3
	13.b	For each group, losses and exclusions after randomization, together with reasons	2-3
Implementation of intervention			
Recruitment	14.a	Dates defining the periods of recruitment and follow-up	9
	14.b	Why the trial ended or was stopped	6
**Baseline data**	15	A table showing baseline demographic and clinical characteristics for each group	not applicable
Numbers analyzed	16	For each group, number of participants (denominator) included in each analysis and whether the analysis was by original assigned groups	10
Outcomes and estimation	17.a	For each primary and secondary outcome, results for each group, and the estimated effect size and its precision (e.g., 95% confidence interval)	10
	17.b	For binary outcomes, presentation of both absolute and relative effect sizes is recommended	10
Ancillary analyses	18	Results of any other analyses performed, including subgroup analyses and adjusted analyses, distinguishing pre-specified from exploratory	10
Harms	19	All important harms or unintended effects in each group; for specific guidance see CONSORT for Harms [60]	9-10
DISCUSSION			
Limitations	20	Trial limitations, addressing sources of potential bias, imprecision, and, if relevant, multiplicity of analyses	12
Generalizability	21	Generalizability (external validity, applicability) of the trial findings	11-12
Interpretation	22	Interpretation consistent with results, balancing benefits and harms, and considering other relevant evidence	11-12
Other information			
Registration	23	Registration number and name of trial registry	1
Protocol	24	Where the full trial protocol can be accessed, if available	1
Funding	25	Sources of funding and other support (e.g., supply of drugs); role of funders	13

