### Randomization and blinding

3.10

Participants will be randomly assigned to two groups in a 1:1 ratio using computer-generated random numbers. During intervention phase, participants will be administered separately in quiet treatment rooms to prevent interactions from different groups. Throughout the study, researchers, acupuncturist, efficacy assessors, and data statisticians will remain segregated. Only the acupuncturist aware of the group assignment result. Participants, evaluators, and analysts will be blinded to group assignments.

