## Outcome measures

5

Each participant will be evaluated by a medical professional blinded to the group assignment and intervention. Assessments will occur at five time points: baseline, 4 weeks, 8 weeks, 12 weeks, and 20 weeks. The schedule of this study is listed in Table 3.

**Table 3 tab3:** Study schedule.

Timepoint	Enrolment	Baseline	Treatment phase		Follow-up phase	
	1 week	0 week	4 weeks	8 weeks	1 month	3 months
Enrolment						
Eligibility screen	**×**					
Medical history	**×**					
Informed consent		**×**				
Allocation		**×**				
Interventions						
Manual acupuncture		**×**	**×**	**×**		
Placebo acupuncture		**×**	**×**	**×**		
Health education		**×**	**×**	**×**		
Assessments						
Demographics	**×**					
fNIRS scanning		**×**		**×**		
PSQI	**×**	**×**				
MoCA	**×**	**×**	**×**	**×**	**×**	**×**
ISI		**×**	**×**	**×**	**×**	**×**
MMSE		**×**	**×**	**×**	**×**	**×**
PHQ-7		**×**	**×**	**×**	**×**	**×**
GAD		**×**	**×**	**×**	**×**	**×**
AES		**×**	**×**	**×**	**×**	**×**
SF-12		**×**	**×**	**×**	**×**	**×**
Safety assessment		**×**	**×**	**×**		
Vital sign		**×**	**×**	**×**		
Use of sleep medications		**×**	**×**	**×**	**×**	**×**

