### Advantages and limitations

9.1

This is the first trial to evaluate the efficacy of acupuncture in CID with MCI. Placebo acupuncture is used to assess the non-specific effectiveness of acupuncture, contributing to deriving more reasonable findings. To stabilize the condition of participants, regular hypnotic medications during the study period will not be restricted. The dosage and frequency of medication will be tracked by evaluators to ensure safety. The study will provide a comprehensive evaluation to assesses effects from multiple aspects, assisting clinical practitioners in accurately assessing effectiveness.

However, there remain limitations. Firstly, due to the specificity of the intervention, blinding of acupuncturists is not feasible. To mitigate potential bias, interventions will be conducted separately in individual rooms. Evaluators responsible for assessing efficacy will be independent of the acupuncturists, data summarizers, and data analysts, ensuring blinding formation. Considering this is an exploratory study aimed at observing the efficacy of acupuncture, further research will consider increasing the sample size to enhance statistical power. Additionally, stratified analyses based on severity or dose-effect analysis could provide a more accurate assessment of acupuncture’s efficacy. Thirdly, the course of acupuncture is a critical factor affecting effectiveness. The 8-week intervention period may not be sufficient for chronic disease. Further studies may extend the acupuncture duration to develop more reasonable cycles. Additionally, acupuncturists are not blinded to the acupuncture prescription. Thus, acupuncturists will be instructed to refrain from discussing treatment plans with patients to minimize potential biases. Due to limited project funding, financial compensation in cash cannot be provided. However, participants will receive personalized health guidance related to insomnia and cognitive function for 5 months. Moreover, the control group will receive free acupuncture treatment after the study concludes. All these provisions have been outlined in the ethics approval.

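### The acupuncturist, the only person who knows the allocation, also gives lifestyle advice: an avoidable risk of performance bias, with the period of guidance stated two ways

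*Protocol article*

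**What the plan says.** **Who advises.** Table 1, STRICTA item 4b, says "the acupuncturist will be responsible for providing treatment and lifestyle advice". Item 4a, on other treatment components in the acupuncture group, reads "Track the regular usage of sleep medications and provide guidance for daily living".

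**Who is unblinded.** Section 3.10 says "Only the acupuncturist aware of the group assignment result", and then "Participants, evaluators, and analysts will be blinded to group assignments".

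**What is promised.** Section 9.1, explaining what is offered in place of cash, says "participants will receive personalized health guidance related to insomnia and cognitive function for 5 months". It names no one to give that guidance.

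**When.** Table 3 has a single row labelled "Health education", not split by arm. It is marked at weeks 0, 4 and 8, with no mark in either follow-up column. Section 5 sets the assessments at "baseline, 4 weeks, 8 weeks, 12 weeks, and 20 weeks".

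**Why there is a sham arm.** Table 1, item 6a, gives the aim as to "explore the specific effects of manual acupuncture on participants".

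**The concern.** A sham control isolates needling only if everything else is delivered alike in both arms. Here the protocol gives a second component, advice, to the one role that cannot be blinded. Section 9.1 describes guidance that is individualised and aimed at sleep and cognition, which the ISI and MoCA measure.

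A provider who knows the allocation may, without intending it, advise one arm more fully than the other. This would be performance bias: the participant really receives something different, so a blinded evaluator would record the resulting difference faithfully and could not remove it. The bias could favour real needling (enthusiasm for the active arm) or work against it (compensating patients known to be on sham).

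The period of guidance matters for a different reason. If guidance continues after needling stops, the course of scores within each group at weeks 12 and 20 mixes continuing guidance with any lasting effect of acupuncture.

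**Working it through.** **1. What each stated safeguard covers**

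| Safeguard | Where | Route it limits | Governs the advice? |
|---|---|---|---|
| Separate treatment rooms | 3.10, 9.1 | Contact between participants of different arms | No |
| Blinded evaluators and analysts, roles kept apart | 3.10, 5, 9.1 | Detection and analysis bias | No |
| Blinded participants | 3.10 | Expectation effects | No |
| Acupuncturists told not to talk about the treatment plan | 9.1 | Disclosure of allocation | No: silent on content and amount of advice |

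The opportunity for unequal contact is real. Table 1 gives 24 sessions with 30 minutes of needle retention each.

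**2. The two periods**

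- Table 3: weeks 0, 4 and 8, so the last mark is at week 8.
- Section 9.1: 5 months, about 20 weeks, which matches the last assessment in section 5.
- Gap: 20 − 8 = 12 weeks, which is the whole follow-up phase.

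**3. The plan's own sample-size inputs (section 3.3)**

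- Planned difference: 3.22 − 1.97 = 1.25 MoCA points.
- Pooled variance: (1.88² + 1.77²)/2 = 3.334, so SD = 1.826.
- n per group = (1.645 + 1.282)² × 2 × 3.334 / 1.25² = 36.5, rounded up to 37.

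The stated 37 is reproduced with a one-sided 5% level and 90% power. This anchors the SD used below. The finding itself does not rest on it.

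**4. Illustration of what unequal advice could do**

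The documents give no effect of guidance on MoCA, so the shift b in the between-arm difference is assumed. Under the normal approximation, with SE = 1.826 × √(2/n):

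- n = 37: SE = 0.425
- n = 45: SE = 0.385

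P(significant) = 1 − Φ(1.96 − b/SE) + Φ(−1.96 − b/SE), for a true needling effect of zero.

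| Assumed shift b | Share of 1.25 | n = 37 | n = 45 |
|---|---|---|---|
| 0 | 0% | 0.05 | 0.05 |
| 0.25 | 20% | 0.09 | 0.10 |
| 0.50 | 40% | 0.22 | 0.25 |
| 0.75 | 60% | 0.42 | 0.50 |

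The same formula covers the opposite direction. Suppose needling truly adds 1.25 points and sham patients are compensated by 0.50, leaving 1.25 − 0.50 = 0.75. Power then falls from 0.84 to 0.42 at n = 37, and from 0.90 to 0.50 at n = 45.

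**The case against.** Four points can fairly be made on the other side.

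- **Both arms seem to get guidance.** Table 3 has one row for both arms and section 9.1 speaks of participants generally. Item 4a mentions only the acupuncture group because that checklist item asks about that group. Guidance delivered equally cancels in the randomised contrast. This stands. A reader might infer that a MoCA or ISI difference could not be attributed to needling at all; the documents do not support that, because nothing says delivery will differ by arm.
- **No one is named for the 5-month guidance.** A reader might join Table 1 to section 9.1 and conclude that the acupuncturist delivers the individualised programme. That is an inference. What is stated is that the acupuncturist gives lifestyle advice. The health education in Table 3 and the guidance in section 9.1 might even be separate activities.
- **An unblinded provider is inherent to manual acupuncture, and a script may sit in the full protocol.** Both are fair. Section 9.1 acknowledges the first openly, and the absence of a script from a condensed article is not the complaint. But giving advice is not inherent to needling, and the article states who gives it.
- **The figures are not the trial's error rates.** This also stands. The shifts are assumed, 45 per group supposes no dropout, and section 7 applies a false-discovery-rate correction that the illustration leaves out.

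**Conclusion.** The point holds as a risk of performance bias that is cheap to reduce. The protocol assigns advice to the only unblinded role, in a trial meant to isolate needling, and none of its stated safeguards governs that advice.

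The size of any bias is unknown and so is its direction. The probabilities above show only how sensitive the comparison would be under assumed shifts of 20% to 60% of the planned effect.

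The mismatch between Table 3 and section 9.1 is an inconsistency to reconcile. It does not bias the between-arm comparison unless the period differs by arm. Its consequence is narrower: if guidance runs through follow-up, within-group changes at weeks 12 and 20, including any paired tests under section 7, should not be read as persistence of an acupuncture effect.

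**What to change.** - During the trial, give advice as one fixed written text or leaflet, identical in both arms.
- Where feasible, have an existing staff member who is blind to allocation deliver it, and take lifestyle advice out of the acupuncturist's role in Table 1, item 4b. Someone who does not rate outcomes is preferable, so that a participant's remarks cannot unblind an evaluator.
- Where that is not feasible, limit the acupuncturist to the fixed text and log advice contacts by arm, so that balance can be reported.
- State in section 9.1 who gives the guidance, and whether it is the same activity as the health education in Table 3.
- Make Table 3 and section 9.1 agree on one period, the same in both arms. The sponsor chooses the period. If it includes follow-up, add a sentence limiting the reading of within-group results at weeks 12 and 20.

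The cost is protocol wording, one leaflet and possibly one reassigned task. Guidance during the trial becomes less tailored. Because section 9.1 says these provisions were set out in the ethics approval, a minor notification to the ethics committee may be needed. Postponing the promised guidance until after week 20 is not necessary.

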## Assessment of safety and “deqi” sensations

6

Vital signs including heart rate, blood pressure, respiration rate, and oxygen saturation will be monitored prior and following each intervention. Any adverse effects (AEs) will be recorded by the operator, with immediate symptomatic treatment and subsequent analysis for causation. Severe AEs will be immediately documented and reported to the Ethics Committee of the Affiliated Hospital of Chengdu University of Traditional Chinese Medicine within 24 h.

We will use an acupuncture sensation scale to assess “deqi” sensations, including soreness, numbness, heaviness, fullness, pain, and anxiety. Participants will also be able to describe any additional sensations they experience. Each sensation will be rated on a 0–10 scale, where 0 indicates no sensation and 10 represents the most intense sensation. Participants will complete this scale after each session, which will facilitate systematic collection and analysis of “deqi” sensations.

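### Table 1 gives randomisation and data collection to one role, in conflict with section 3.10; separately, adverse events are recorded by the unblinded operator

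*Protocol article*

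**What the plan says.** **Roles.** Item 4b of Table 1 names three groups. Researchers diagnose and obtain consent, the acupuncturist treats and advises, and "designated researchers will be responsible for randomization and data collection".

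**Blinding.** Section 3.10 states that "researchers, acupuncturist, efficacy assessors, and data statisticians will remain segregated", that "Only the acupuncturist aware of the group assignment result", and that "Participants, evaluators, and analysts will be blinded to group assignments". Section 5 adds: "Each participant will be evaluated by a medical professional blinded to the group assignment and intervention". Section 9.1 makes the efficacy evaluators independent of the acupuncturists, of those who summarise the data and of the analysts.

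**Harms.** Section 6 states: "Any adverse effects (AEs) will be recorded by the operator, with immediate symptomatic treatment and subsequent analysis for causation". Item 6 of Table 1 makes the operators, who apply the needles, the exception to blinding.

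**The concern.** A person who runs a 1:1 randomisation and passes on the result ordinarily knows it. Table 1 gives that task and data collection to one named role, while section 3.10 allows nobody but the acupuncturist to know the assignment. Followed as written, the two cannot both hold unless something stops the randomising staff from seeing what they assign, or unless different people do the two tasks. The article says neither.

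The blinding of data handling is at stake. MoCA, the primary outcome, is scored by a rater, and most of the secondary scales rest on self-report or informant report. Such data are best kept away from anyone who knows the arm.

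The harms issue is different in kind. The person who decides what is written down as an adverse event has just applied a penetrating or a blunt needle. The threshold for recording a minor event can then differ by arm without any intent. Severe safety issues are a termination criterion (section 3.9), and the Data Monitoring Committee reviews safety data (section 3.11), so these records carry weight.

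**Working it through.** The plan gives no figure on this point. The check compares the statements on roles.

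1. **Who knows the assignment.** Section 3.10: the acupuncturist only. Table 1 item 4b: the designated researchers carry out the randomisation. These agree only if the randomising staff do not see the result.

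2. **Whether the randomising staff are covered by a safeguard.** The blinded list in section 3.10 names participants, evaluators and analysts. The independence statement in section 9.1 separates evaluators from acupuncturists, data summarisers and analysts. Neither names those who randomise. Section 3.10 does separate researchers from efficacy assessors, but it does not separate the randomising task from the data-collection task.

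3. **What the Table 1 sentence can mean.**
   - (a) Different designated researchers do each task. The data collectors may then be blind, but the text does not say so.
   - (b) The same people do both, and data collection means gathering and entering forms scored by others. They can know the arm while handling data, but they do not produce the scores.
   - (c) The same people do both and also administer the scales. This would contradict the blinded-evaluator statements in sections 3.10 and 5 and the segregation rule.

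   Readings (a) and (b) remain open. Reading (c) needs a breach of other stated rules.

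4. **Order at week 0.** Table 3 puts allocation, the baseline scales and the baseline scan in the same week-0 column and gives no sequence. If allocation comes first, a collector who knows it could be present for baseline measurements.

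5. **Adverse events.** The recorder is the operator (section 6). The operator is not blinded (Table 1 item 6). No other recorder of adverse events is named.
   - Sessions per participant: 24 (Table 1 item 3a).
   - Participants: 45 per arm, 90 in all (section 3.3).
   - Planned sessions: 45 × 24 = 1,080 per arm; 90 × 24 = 2,160 in total.

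   All of these sessions have an unblinded recorder.

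6. **Whether step 5 contradicts step 1.** It does not. The operator is the acupuncturist, the one person whom section 3.10 allows to know the arm. It is a separate weakness.

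**The case against.** Several points count against a stronger version of this concern, and most of them stand.

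- **A reader might infer that MoCA scores are biased and the false-positive rate inflated.** The documents do not support this. Sections 3.10 and 5 state that evaluators are blinded, and nothing says that the designated researchers score any scale. Any assumed size of rater bias would have no source in the article, so a false-positive rate built on it would only be illustrative. None is given here.
- **A reader might infer that operator-recorded adverse events break the rule that only the acupuncturist knows the arm.** They do not, as step 6 of the working shows.
- **A reader might infer unequal lifestyle advice**, since "the acupuncturist will be responsible for providing treatment and lifestyle advice". No statement says that advice differs by arm. Table 3 schedules health education without distinguishing arms, and section 9.1 promises guidance to participants generally.
- **Enrolment is already a separate role.** Table 1 lists the staff who diagnose and obtain consent apart from the designated researchers. Details of envelopes or a central list are commonly left to the full protocol, so their absence is not counted as a fault.
- **Some mitigation exists.** Participants, who are blinded, rate sensations including pain after every session. An independent committee monitors safety, and section 9.1 admits that acupuncturists are unblinded.

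The mitigation is partial. The sensation scale is meant to measure deqi and is not an adverse-event record. The committee sees only what has been recorded. Section 9.1 discusses bias in efficacy assessment but not in the recording of harms. The mismatch between Table 1 and section 3.10 and the unblinded harms recording therefore both remain.

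**Conclusion.** The point holds in two separate parts.

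First, Table 1 item 4b and section 3.10 conflict on who may know the assignment, and no stated safeguard names the randomising staff. The consequence for efficacy data is conditional: it arises only if the same people both randomise and collect data, and it reaches the MoCA scores only if they also score or influence the scales. Its size cannot be estimated from the documents.

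Second, adverse events are recorded by an unblinded person at every one of the 2,160 planned sessions, so a between-arm difference in recorded harms, or the lack of one, could reflect recording habits. The direction and size are unknown because the article gives no expected event rates. This rests on reading operator as the person who applies the needles, as Table 1 item 6 does.

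Both parts can be corrected cheaply and should be.

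**What to change.** 1. Amend Table 1 item 4b so that the sequence is held by existing staff with no enrolment, data-collection or outcome-assessment duty. Each assignment is released only to the acupuncturist, after the week-0 assessments and any baseline scan are complete. Amend section 3.10 to name this role, so that the two places agree.
2. In section 6, add a standard adverse-event checklist completed by the blinded participant at existing visits, for example together with the sensation scale already filled in after each session. Keep the operator's log as a supplement.
3. Keep the checklist from the MoCA rater, or have it completed only after MoCA is scored. Answers about the needle site could reveal the arm, because real needles penetrate the skin and blunt ones do not.

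The cost is a reassignment of duties among existing staff, a one-page form and slightly more participant time. No new visits are needed, and needling and lifestyle advice are unchanged.
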